## Abstract

**Introduction:**

People with involvement in forensic psychiatric services face many obstacles to employment, arising from their offending, as well as their mental health problems. This study aims to assess the feasibility of conducting a randomised controlled trial (RCT) to evaluate the effectiveness of individual placement and support (IPS), in improving employment rates and associated psychosocial outcomes in forensic psychiatric populations. IPS has been found consistently to achieve employment rates above 50% in psychiatric patients without a history of involvement in criminal justice services.

**Methods/design:**

This is a single-centre feasibility cluster RCT. Clusters will be defined according to clinical services in the community forensic services of Nottinghamshire Healthcare NHS Foundation Trust (NHCT). IPS will be implemented into 2 of the randomly assigned intervention clusters in the community forensic services of NHCT. A feasibility cluster RCT will estimate the parameters required to design a full RCT. The primary outcome is the proportion of people in open employment at 12-month follow-up. Secondary outcome measures will include employment, educational activities, psychosocial and economic outcomes, as well as reoffending rates. Outcome measures will be recorded at baseline, 6 months and 12 months. In accordance with the UK Medical Research Council guidelines on the evaluation of complex interventions, a process evaluation will be carried out; qualitative interviews with patients and staff will explore general views of IPS as well as barriers and facilitators to implementation. Fidelity reviews will assess the extent to which the services follow the principles of IPS prior, during and at the end of the trial.

**Ethics and dissemination:**

Ethical approval was obtained from the East Midlands Research Ethics Committee-Nottingham 1 (REC reference number 15/EM/0253). Final and interim reports will be prepared for project funders, the study sponsor and clinical research network. Findings will be disseminated through peer-reviewed journals, conferences and event presentations.

**Trial registration number:**

NCT02442193; Pre-results.

Strengths and limitations of this studyThis study will be the first in the UK to consider how best individual placement and support (IPS) can be adapted for patients with offending histories.Our study will provide commissioners with a full understanding of how IPS could be implemented in forensic mental health settings elsewhere and provide information about the key parameters needed to design a full RCT.This study is a small-scale, single-centre study. The study is a feasibility trial and as such does not allow us to draw conclusions about the efficacy of IPS.

## Introduction

Unemployment has a number of undesirable consequences and has been linked to low personal well-being,^1^ poor physical and/or mental health^2^ and can serve to exacerbate these pre-existing health conditions.^3^ Besides income, work is also widely recognised as being beneficial to an individual's mental health^2^
^4^ and can enhance a person's self-esteem and inspire optimism.^4^

People with severe mental disorders have far higher rates of unemployment when compared with the general population^5^ and are more likely to be unemployed compared with the general disabled population.^6^ Recent Department for Work and Pensions’ (DWP) figures show that 6.5 million working-age people in the UK are classified as disabled under the Equality Act 2010 because they have a physical or mental condition that affects their ability to carry out daily activities.^7^ However, many of these people can work and the employment aspirations of many remain unfulfilled. Use of supported employment, to help with this issue, has been consistently advocated in public policy.^7^

Furthermore, employment rates for offenders are also worryingly low, with the Ministry of Justice and DWP^8^ reporting that 29% of prisoners found paid employment at some point in the 2 years following their release and that only 15% were in paid employment 2 years after their release. Government initiatives have also emphasised the importance of using work to reduce reoffending rates among offenders.^9^ Offending history is further compounded by the fact that the prevalence of mental disorders among offenders is far greater than in the general population.^10^

Offenders with mental disorders arguable fare worse in regards to employment partly due to the stigma attributed to their offending history and negative stereotypes of people with mental health problems on the part of employers and members of the public.^11^ Complex personal and social problems, including homelessness, substance misuse, lack of relevant skills or qualifications and limited employment experience, make it even more difficult for them to secure employment.^12^

There is strong evidence in favour of individual placement and support (IPS), a well-established form of supported employment, as the most effective approach to help people with severe mental disorders get back into employment.^5^
^13–17^ IPS operates according to the following principles: (1) it aims to get people into competitive employment; (2) it is open to all those who want to work; (3) it tries to find jobs consistent with people's preferences; (4) it works quickly; (5) it brings employment specialists into clinical teams; (6) employment specialists develop relationships with employers based on a person's work preferences; (7) it provides time unlimited, individualised support for the person and their employer; and (8) benefits counselling is included.

The Cochrane review by Kinoshita *et al*,^5^ including 14 randomised controlled trials (RCTs) (2265 participants in total), showed that IPS significantly increased levels of employment and increased length of competitive employment for individuals with severe mental illness, when compared with other vocational approaches. Although the literature supports the effectiveness of IPS in generic mental healthcare settings, the evidence base for its effectiveness in forensic mental health settings is lacking.^18^ A paper commissioned by the Sainsbury Centre for Mental Health,^19^ which reviewed the literature on employment support for offenders with mental health problems, concluded that many principles of IPS, if suitably adapted, have the potential to help offenders with mental disorders gain employment. However, it is not known how best to adapt IPS to forensic mental health settings, and to the best of our knowledge, no empirical studies of IPS in UK community forensic mental health settings have been completed to date.

IPS can be regarded as a complex intervention as it involves a number of interacting components. Developing an evidence base for IPS in a forensic mental health setting adds to this complexity, since the management of mentally disordered offenders combines various treatment modalities to address mental health issues, offending behaviour and risk management.^20^ Nevertheless, little attention, particularly in the health sector, is paid to supporting mentally disordered offenders into mainstream employment. It is the very complexities in the practice of forensic mental health, which make the implementation and evaluation of IPS a challenge; the present study is, therefore, needed to underpin robust future RCTs, so that this intervention, proven to be effective in adults with mental health problems, can be appraised for its potential to enable patients with offending histories to live more rewarding lives, reduce reoffending and minimise their dependency on formal services. It is hypothesised that the benefits of IPS found in adult mental health settings will be replicated to some degree in the forensic population. The proposed study will, therefore, bring benefits to patients, to the local service, to national forensic and mental health services and will inform commissioning and policymakers.

## Aims and objectives

The overall aim of the study is to assess the feasibility of conducting a fully powered RCT to evaluate the effectiveness of IPS in improving employment rates and associated psychosocial outcomes in community forensic psychiatric populations.

The specific objectives of the study are as follows:
To estimate the parameters required to design a full RCT, including means and SDs, of the key outcome measures in order to benchmark potential effect sizes and enable sample size calculations.To assess the feasibility of randomisation, recruitment and retention rates to the IPS and control arms.To explore the suitability of the key outcome measures with respect to reliability, acceptability and distribution of the scores.

A process evaluation will also be carried out; qualitative interviews with patients and staff will explore general views of IPS as well as barriers and facilitators to implementation, while fidelity reviews will assess the extent to which the services follow the principles of IPS.

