#### Randomisation: sequence generation

Randomisation of clusters was carried out by the trial statistician from the University of Leicester Clinical Trials Unit, allocating two clusters (City Community Forensic Service and the County Personality Disorder Service) to the intervention group (IPS+treatment as usual [TAU]). The remaining two clusters (County Community Forensic Service and City Personality Disorder Service) were allocated to the control group (TAU) (figure 1 for trial flow chart).

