#### Sample size

The sample size calculation was based on an assertion by Eldridge and Kerry^23^ that, for samples of 75–150 individuals, four clusters will be required to achieve reasonably precise 95% CI for intraclass correlation coefficient (ICC). We aim to recruit a total sample size of 76 individuals for the trial.

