#### Planned analysis and study data

Analysis will be conducted on a treatment allocated basis. We will describe recruitment and retention rates, ICCs of outcome measures (primary and secondary) and patterns of missing data. We will provide means and SDs for continuous outcomes and percentage proportions for categorical outcomes with CIs. Comparisons between the two arms will be made for the outcome measures administered to estimate potential magnitude of effect.

It must be acknowledged that estimating ICCs with small numbers of participants can potentially result in biased or imprecise estimates. Because of this, the feasibility study will not be the only source to estimate ICCs. Published or unpublished data of similar outcomes in adult mental health settings in the UK will also be used to estimate ICCs.

Monitoring of study data shall include confirmation of informed consent, source data verification, data storage and data transfer procedures, local quality control check and procedures, back-up and disaster recovery of any local databases and validation of data manipulation. All data held electronically concerning the primary outcome variables will be checked against the paper record for accuracy. Ten per cent of the remaining data will be checked in the same way. Where corrections are required, these will carry a full audit trail and justification.

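### The difference between two clusters per arm is given a role in benchmarking the full trial's effect size, with no safeguard like the one set for the ICC

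*Protocol article*

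**What the plan says.** Under Aims and objectives, the first specific objective is to estimate the design parameters of a full RCT, including means and SDs of the key outcomes, "in order to benchmark potential effect sizes and enable sample size calculations". Planned analysis and study data adds: "Comparisons between the two arms will be made for the outcome measures administered to estimate potential magnitude of effect".

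The same analysis section concedes that ICCs from few participants may be biased or imprecise, and says other published or unpublished data will also be used for them. It says nothing similar about the effect size.

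The Sample size section rests on a cited rule about ICC precision: "for samples of 75–150 individuals, four clusters will be required to achieve reasonably precise 95% CI for intraclass correlation coefficient (ICC"). The target is 76. Randomisation produced two clusters per arm, "allocating two clusters (City Community Forensic Service and the County Personality Disorder Service) to the intervention group" and the other two services to control. The strengths and limitations box states that the study "does not allow us to draw conclusions about the efficacy of IPS".

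**The concern.** Estimating SDs, the control-arm rate, ICCs, recruitment and retention is proper work for a feasibility study. The observed difference between arms is another matter. It comes from four teams, and the sample size was chosen for the ICC, not for this contrast.

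The layout adds to the difficulty. Each arm holds one community forensic team and one personality disorder team, one from the city and one from the county. Area and service type therefore balance as main effects, but arm is aliased with the area-by-service interaction. Whatever is peculiar to a particular team cannot be separated from the effect of IPS.

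If such a difference sets or anchors the effect size, an overestimate yields an underpowered full trial and an underestimate yields a needlessly large one. The authors saw this danger for the ICC and guarded against it. The effect size, which usually moves a sample size at least as much, has no such guard.

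**Working it through.** **The plan's own figure.** The target of 76 comes with no alpha, power, effect, SD, ICC or interval width, so it cannot be recomputed. It does lie within the cited 75–150 with four clusters, and 76/4 = 19 per cluster, 38 per arm.

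**Inputs.** From the article: 76 people, four clusters, two per arm, binary primary outcome (open employment at 12 months). Assumed, because the article gives no design values: equal clusters of 19, true rates 40% v 20%, ICC 0.02 to 0.05. As a second case, 50% v 15%: the abstract's rate for IPS in non-forensic patients and the introduction's rate for released prisoners at 2 years. Both are proxies.

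**Precision of the difference, 40% v 20%.**
- Ignoring clustering: SE = sqrt[(0.4×0.6 + 0.2×0.8)/38] = sqrt(0.40/38) = 0.103. Half-width 1.96 × 0.103 = 0.20.
- Design effect = 1 + (19 − 1) × ICC, that is 1.36 at ICC 0.02 and 1.90 at ICC 0.05. SE = 0.120 and 0.141. Half-widths with z: 0.23 and 0.28.
- Four clusters less two arms leave 2 degrees of freedom, t = 4.303. Half-widths: 0.51 and 0.61.

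**How far one study can stray.** In a beta-binomial simulation (two clusters of 19 per arm, true 40% v 20%, ICC 0.02), the middle 80% of observed differences runs from 5 to 34 points. About 6% are zero or negative. About 20% overstate the true 20 points by half or more.

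**Consequence for the full trial** (two-sided 5%, 90% power, before any design effect). N per arm = (1.96 + 1.2816)² × [p1(1−p1) + p0(1−p0)]/(p1−p0)².
- True 40% v 20%: 10.51 × 0.400/0.04 = about 105.
- Sized on 45% v 15%, a 1.5-fold overestimate: 10.51 × 0.375/0.09 = 43.8, so 44.
- Power of 44 per arm at the true effect: Φ(0.20/sqrt(0.40/44) − 1.96) = Φ(0.14) = about 0.55.

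**Sensitivity to the rates** (ICC 0, 80% power, pooled-variance formula, observed difference one SE either side of the truth, control rate held at 15%).
- 50% v 15%: SE = sqrt(0.3775/38) = 0.100. Observed 45 or 25 points gives 17 or 49 per arm, against 27.
- 30% v 15% (the 30% is an assumed diluted effect): SE = sqrt(0.3375/38) = 0.094. Observed 24 or 6 points gives 51 or 738 per arm, against 121.

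The problem is mild if the effect is as large as in general psychiatry and severe if it is diluted.

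**The case against.** The best defence is that the text is modest. It speaks of benchmarking and of potential effects, names means and SDs (ordinary feasibility outputs), and disclaims any conclusion on efficacy. The introduction already cites a review of 14 IPS trials that could inform the target. Much of this stands, and it rules out several stronger readings that a reader might infer:

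- *The full trial will be powered on the pilot difference alone.* No sentence says so. The article gives the difference a role and does not say how much weight it carries.
- *A low pilot difference would lead to abandonment.* The four feasibility criteria in the Discussion concern recruitment, intervention completion, acceptability and completeness of outcome data. None uses the effect.
- *The analysis will give intervals that are too narrow, or p values, for the difference.* The article attaches confidence intervals to the descriptive summaries, specifies no individual-level interval for the difference and plans no tests. How an interval handles clustering can be left to an analysis plan that is not shown.
- *The disclaimer on efficacy contradicts the comparison.* Describing a possible magnitude is compatible with drawing no conclusion from it.

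What the defence does not answer is the stated purpose. Means and SDs by arm, compared to estimate magnitude and collected to benchmark effect sizes for a sample size calculation, are a use of the difference. No passage limits that use or names another source for the target.

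**Conclusion.** The point holds in limited form. The objectives and the analysis section let the observed difference benchmark the full trial's effect size, and the imprecision caveat stops at the ICC. The conclusion does not depend on clustering: the 95% half-width of about 20 points without it is as large as the assumed true effect of 20 points, and the 2 degrees of freedom make it far wider.

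The sizes rest on assumed rates, ICCs and equal clusters. Under the more favourable 50% v 15% the derived sample size still varies almost threefold (49/17 = 2.9) within one SE. It is worth correcting, because it bears on the design of the definitive trial and costs only wording. It does not undermine the feasibility study itself.

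**What to change.** - In the first objective, remove the benchmarking of effect sizes from the observed difference.
- There and in the analysis section, state that the full RCT's target difference will come from a minimum important difference and published IPS evidence. This study supplies the control-arm rate, SDs, ICCs (with the external data already planned), recruitment and retention.
- Report the overall difference between arms descriptively, with any interval allowing for clustering on 2 degrees of freedom.
- Show contrasts within service type, if at all, without intervals. Each has one cluster per arm, so no degrees of freedom remain for a cluster-level interval.

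The cost is a few sentences and no new data. The drawback is that the study no longer offers its own effect-size estimate for planning.

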## Methods/design

The design of this study has drawn from the principles set out in the Medical Research Council Guidance^21^ on developing and evaluating complex interventions by using three major strands with clearly defined time scales as follows.

### Implementation of IPS in community forensic services (6 months)

A fundamental prerequisite to IPS research is appropriate implementation. This study will, therefore, allocate 6 months to embedding the IPS model within the intervention clusters. IPS will be embedded by bringing an employment specialist into the clinical teams, raising awareness about IPS within the organisation and forming links with IPS services within the local National Health Service (NHS) Trust, in addition to developing important links with employers and the DWP. This process of implementation is guided by prior work in adult mental health and led by a dedicated development team.^22^

### Feasibility study (24 months)

#### Participants and study design

This study will recruit adult patients (male and female) who are over the age of 18 and who are currently on the caseload of the community forensic services. Patients who are unable to provide informed consent, who are not eligible to work in the UK, do not have an offending history, are currently in open employment or who do not wish to work will be excluded from this study.

This study employs a cluster RCT design. Clusters are defined according to clinical services in the community forensic services, which include four major divisions as follows: Cluster 1: City Community Forensic Service. Cluster 2: County Community Forensic Service. Cluster 3: City Personality Disorder Service. Cluster 4: County Personality Disorder Service.

#### Randomisation: sequence generation

Randomisation of clusters was carried out by the trial statistician from the University of Leicester Clinical Trials Unit, allocating two clusters (City Community Forensic Service and the County Personality Disorder Service) to the intervention group (IPS+treatment as usual [TAU]). The remaining two clusters (County Community Forensic Service and City Personality Disorder Service) were allocated to the control group (TAU) (figure 1 for trial flow chart).

**Figure 1 BMJOPEN2016012710F1:**
[figure not shown]
Trial flow chart. IPS, individual placement and support; TAU, treatment as usual.

#### Interventions

Group 1: Individuals assigned to the intervention group will receive IPS+TAU. Individuals will receive ongoing support from the employment specialist in accordance with the IPS principles. The employment specialist will work closely with patients assigned to IPS and begin job searches rapidly, based on their preferences. Colocation of the employment specialist within clinical teams will allow information about risks and past offending histories to be shared with employers (with patient's consent), health and criminal justice systems (for those concurrently under probation) and subsequently taken into consideration when matching job opportunities to individual preferences. The employment specialist will bridge the gap between the research team and the community forensic teams by virtue of being a member of both teams.

Group 2: Individuals assigned to the control group will not receive any IPS support but will continue to receive TAU from the community forensic services. TAU for patients who are part of the city or county forensic teams entails case management, where each individual is allocated a consultant and care coordinator. TAU for patients who are part of the City or County Personality Disorder teams will primarily be made up of therapy services providing specialised psychological interventions, including group therapy and attendance, at a therapeutic community. Neither groups are offered specialist employment support as part of TAU.

#### Sample size

The sample size calculation was based on an assertion by Eldridge and Kerry^23^ that, for samples of 75–150 individuals, four clusters will be required to achieve reasonably precise 95% CI for intraclass correlation coefficient (ICC). We aim to recruit a total sample size of 76 individuals for the trial.

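### N = 76 is justified only by a reasonably precise 95% CI for the ICC, which four clusters do not give: at an assumed ICC of 0.05 it runs from about 0 to 0.59 or 0.80

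*Protocol article*

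**What the plan says.** The Sample size section of the protocol article rests on a cited assertion that, with 75 to 150 people, "four clusters will be required to achieve reasonably precise 95% CI for intraclass correlation coefficient (ICC". It then sets the target: "We aim to recruit a total sample size of 76 individuals for the trial". It gives no assumed ICC, interval width or calculation.

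Participants and study design fixes the number of clusters: "Clusters are defined according to clinical services in the community forensic services, which include four major divisions". They are a city and a county community forensic service and a city and a county personality disorder service. Under Randomisation: sequence generation, each arm receives two clusters, one of each service type: "The remaining two clusters (County Community Forensic Service and City Personality Disorder Service) were allocated to the control group (TAU".

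Planned analysis and study data says that ICCs will be described for primary and secondary outcomes. It then warns that "estimating ICCs with small numbers of participants can potentially result in biased or imprecise estimates", and for that reason says that published or unpublished data on similar outcomes in UK adult mental health settings will be used as well.

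**The concern.** An ICC compares variation between clusters with variation within them. How well the between-cluster part is estimated depends mainly on the number of clusters, and here there are four, two per arm. That leaves 3 between-cluster degrees of freedom, or 2 once arm is allowed for. A sample size whose only rationale is ICC precision therefore looks unsupported. The analysis section in effect withdraws the precision that the Sample size section claims, and the two cannot both stand.

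At stake is the reason given for 76, and how much weight the trial's own ICC receives when a later trial is planned. The first objective is to supply parameters that enable sample size calculations. A reader who takes the precision claim at face value may trust an internal ICC that carries very little information.

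**Working it through.** **The plan's own figure.** N = 76 cannot be reproduced, because no ICC, width or formula is given. It only lies inside the quoted range of 75 to 150.

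**Inputs.** From the document: k = 4 clusters, N = 76, 95% two-sided confidence, two clusters per arm. Assumed: equal clusters, so m = 76/4 = 19, and a set of ICC values, since the document states none. Within-cluster df: d2 = 76 - 4 = 72. Between-cluster df: d1 = 3 ignoring arm, 2 adjusting for arm.

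**Formula (exact one-way ANOVA interval).** F = (1 + (m - 1) x ICC)/(1 - ICC); FL = F/F(.975; d1, d2); FU = F x F(.975; d2, d1); each limit is (F* - 1)/(F* + m - 1), with F* = FL or FU.

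**At an observed ICC of 0.05.** F = (1 + 18 x 0.05)/0.95 = 2.00.

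- 3 df: FL = 2.00/3.303 = 0.605, lower limit -0.395/18.605 = -0.02. FU = 2.00 x 13.977 = 27.95, upper limit 26.95/45.95 = 0.59.
- 2 df: FL = 2.00/3.885 = 0.515, lower limit -0.485/18.515 = -0.03. FU = 2.00 x 39.484 = 78.97, upper limit 77.97/96.97 = 0.80.

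**Over a range of ICCs (N = 76).**

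| Observed ICC | 3 df, arm ignored | 2 df, arm adjusted |
|---|---|---|
| 0.01 | -0.03 to 0.45 | -0.04 to 0.71 |
| 0.05 | -0.02 to 0.59 | -0.03 to 0.80 |
| 0.10 | -0.00 to 0.69 | -0.01 to 0.87 |
| 0.20 | 0.04 to 0.81 | 0.02 to 0.92 |

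**Top of the quoted range.** With N = 150 (m = 37.5, d2 = 146) and ICC 0.05, the interval is -0.00 to 0.52 (3 df) or -0.01 to 0.76 (2 df).

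**Chance of an estimate at or below zero.** This is P(F(d1, d2) < (1 - ICC)/(1 + (m - 1) x ICC)). With a true ICC of 0.05 and N = 76, it is P(F < 0.50) = 32% (3 df) or 39% (2 df). With N = 150 it falls to 20% or 29%.

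**Is a different method kinder?** The large-sample standard error gives 0.05 +/- 0.16 (3 df) or +/- 0.19 (2 df), which looks tighter. In 200,000 simulated draws those nominal 95% intervals covered the true value only about 78% and 73% of the time, so they do not rescue the claim.

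**Binary outcome.** The exact interval assumes normality, and the primary outcome is a proportion. An arm-adjusted beta-binomial simulation at ICC 0.05 gave an estimate at or below zero in about 40% of runs, against 39% above.

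**Service type.** The section on interventions gives the forensic and personality disorder services different usual care. An ICC across all four services absorbs any fixed difference between the two types. For illustration, with employment of 40%, 40%, 20% and 20%, the between-service variance (divisor 3) is 0.0133 and the mean within-service variance is (0.24 + 0.16)/2 = 0.20, so the apparent ICC is 0.0133/0.2133 = 0.06 from that difference alone. Removing service type as well as arm leaves 1 df, the city versus county contrast. At ICC 0.05 the interval is then -0.03 to 0.99.

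**The case against.** The strongest reply is that the document already deals with this. It warns of biased or imprecise ICCs and commits to outside data, so a later trial would not be sized on this ICC alone. That stands, and it limits the harm. A reader might infer that the full trial would be mis-sized; the analysis section does not support that. What survives is that outside data are an addition, with no statement of how much weight the internal ICC keeps.

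A reader might also infer that the ICC cannot be estimated, or that the study's main parameter is lost. Neither follows. An ICC can be computed, only not with useful precision. The objectives name means, SDs, recruitment and retention, and none of the four feasibility criteria in the Discussion uses an ICC. The document does not even fix a cluster design for the full trial.

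Nor is it right that the number of participants is irrelevant. Going from 76 to 150 people lowers the chance of an estimate at or below zero from 32% to 20% (3 df), and at an observed ICC of 0.01 lowers the 3 df upper limit from 0.45 to 0.33. Clusters dominate, but participants contribute, so the caveat is incomplete rather than false.

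Finally, the rationale cites a source that was not available here. Whether it is quoted correctly, and what it means by reasonable precision, was not checked. The point concerns only the property that the protocol claims for its own design.

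**Conclusion.** The point holds in limited form. The sole stated reason for N = 76 is a design property that four clusters do not deliver. At an observed ICC of 0.05 the arm-adjusted 95% CI runs from about 0 to 0.80, and ignoring arm from about 0 to 0.59. No ICC between 0.01 and 0.20 gives a usefully narrow interval, and neither does the upper end of the quoted sample range at an ICC of 0.05. The Sample size and Planned analysis sections contradict each other on this, and the caveat leaves out the larger cause.

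The conclusion assumes equal cluster sizes, normal theory and ICC values that the document does not give. The upper limit moves with the assumed ICC, and at 0.20 the lower limit rises above zero. If only half of the participants have complete data, the lowest level that the Discussion would accept, then 38 are analysed and the upper limits at ICC 0.05 become 0.68 and 0.86. None of this shows that 76 is the wrong number for a feasibility study, only that the reason given for it fails.

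**What to change.** - **Sample size:** remove the claim of a reasonably precise ICC interval. Justify 76 by the precision of recruitment, retention, completion and employment proportions. For example, a proportion near 50% among 76 people has a 95% half-width of 1.96 x sqrt(0.25/76) = 11 points ignoring clustering, or 11.2 x sqrt(1.9) = 15 points with the design effect 1 + 18 x 0.05 = 1.9. The recruitment rate needs its own calculation, since its denominator is referrals.
- **Expected ICC interval:** state it with its assumed ICC and degrees of freedom, for instance about 0 to 0.8 at ICC 0.05, adjusted for arm.
- **Planned analysis:** treat the trial's ICCs as descriptive and report them with CIs. Take the ICC for the full trial mainly from the external data already planned, over a stated range. Attribute the imprecision to few clusters as well as few participants.
- **Service type:** note that an ICC across the four services includes the forensic versus personality disorder difference, and that removing it leaves 1 df and an essentially uninformative interval.

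The cost is wording and a less favourable stated precision. No extra patients are needed, and the primary outcome and feasibility criteria do not change.
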